## Study site

The study will be carried out in three provinces in southern Mozambique (Maputo City, Maputo Province and Gaza Province), where the following hospitals will be selected for convenience: Maputo Central Hospital (MCH), Mavalane General Hospital (MGH), José Macamo General Hospital (JMGH), Matola Provincial Hospital (MPH), Xai-Xai Provincial Hospital (XPH) and Carmel Hospital of Chokwé (CHC). These are the most distinguished hospitals in the southern part of the country.

**Description of each study site:**

MCH is a reference hospital in the country, located in the city of Maputo, in the Central neighbourhood. It is situated between [name]. It is a quaternary level hospital and the most differentiated in the country, with University Hospital status; MGH is a tertiary level hospital and is located in the city of Maputo, KaMavota Urban District, Mavalane neighbourhood, on [name]; JMGH is a tertiary level hospital and is located on [name], Nlhamankulu Urban District in Maputo; HPM is a tertiary level hospital and is located in Matola City, Maputo Province; HPX is a tertiary level hospital and is located in Xai-Xai City, Gaza Province; HCC is a tertiary level hospital located in the district of Chokwé, is a reference centre for Tuberculosis and AIDS patients in Gaza Province, and is managed and administered by the Sisters of Charity of St Vincent de Paul, by agreement with the MoH.

In terms of capacity, the hospitals selected for the study operate with a capacity of approximately (239-1500) official beds and have the following clinical services: medicine, orthopaedics, paediatrics, surgery, gynaecology-obstetrics, oncology, emergency and resuscitation services. They are NHS hospitals and are managed by the MoH. It should be noted that Hospital Carmelo, a referral hospital for tuberculosis and AIDS patients, is managed and administered by the Sisters of Charity of St Vincent de Paul, in agreement with the MoH. The hospitals were selected for convenience (existence of a research partnership agreement for many years, they have HIV and inpatient services).

## Study timeline

- The study will last approximately 1 year and 3 months with different phases:
- First phase: Assessment of the current situation: (duration 3 months):
- Second phase: Adaptation (duration 3 months);
- Third phase: Implementation of the intervention in phases guided by the PAD (duration 6 months);
- Fourth phase: Evaluation, sustainability and results according to the RE-AIM (duration 3 months).

## Study population

- Doctors, nurses, and laboratory technicians from the following hospitals: MCH, MGH, JMGH, MPH, XPH and CHC.

## Sample and Sampling

**Sample for the qualitative component of the study**

The sample size will be determined based on two principles: previous studies of the implementation of techniques in hospitals and theoretical saturation. The sample in previous studies ranges from ‘24-30 health professionals’. Since Mozambique has a shortage of health professionals, it was determined that all available professionals (doctors, nurses and laboratory technicians) working in the medicine and microbiology laboratories of the selected hospitals would be involved in the study.Profissionais por serem envolvidos

MCH: 8 clinicians from Medicine and 2 laboratory technicians;

MGH: 4 clinicians from Medicine and 2 laboratory technicians;

HGJM: 4 clinicians from Medicine and 2 laboratory technicians;

MPH: 3 clinicians from Medicine and 2 laboratory technicians;

XPH: 3 clinicians from Medicine and 2 laboratory technicians;

CHC: 2 clinicians from Medicine and 2 laboratory technicians.

.

**Sampling**

Sampling will be non-probabilistic, with participants selected intentionally and study sites (hospitals) selected for convenience. The involvement of the selected hospitals is due to the existence of a research partnership agreement with them for many years, and they also have medical services associated with ART and hospitalisation, which is a great advantage for the implementation of this study.

The researcher will have no contact with the patients and will not recruit them. The clinician will decide which patients to ask for urine samples to diagnose cryptococcosis. The study will provide the national health system with a resource for diagnosing cryptococcosis.Descrição da técnica a ser implementada

## The India ink in urine technique is a quantitative, low-cost, easy-to-perform and easy-to-maintain technique. It is carried out using a non-invasive sample (urine) that is easy to obtain. A drop of urine of approximately 2ml is deposited on the microscope slide, and then a drop of China ink is added and covered with the coverslip. The result is obtained in approximately 15 minutes and allows capsulated yeasts suggestive of Cryptococcus spp. to be observed.

## 7.6. Inclusion and exclusion criteria

**7.6.1. Inclusion criteria**

- Laboratory technicians assigned to the Microbiology sector, doctors and nurses assigned to the medical services of each selected hospital will be included.

**7.6.2. exclusion criteria**

- All health professionals who are not directly involved in the microbiological diagnosis and care of adult HIV patients will be excluded.

**7.8. Procedures, instruments for collecting and analysing data**

Quantitative data will be collected by the researcher based on the observation guide and questionnaire attached to the REDCap platform loaded onto the tablet. Demographic information will be collected from the professionals, and all the equipment and materials currently in use for the care and treatment of cryptococcosis will be listed and described, including the collection of information related to the infrastructure of each health unit.

It will also describe the cryptococcosis diagnoses currently carried out in each hospital involved in the study and identify barriers and facilitators to the implementation of the cryptococcosis diagnosis technique using urine samples.

Based on the DAP conceptual framework, laboratory diagnosis of cryptococcosis will be implemented in the six selected hospitals, training will be carried out, a flow of information will be created between laboratory technicians and clinicians, the definition of a cryptococcosis case will be standardized and diagnostic and treatment guidelines will be provided.

During implementation, clinicians will request urine samples from eligible patients and will be performed by trained laboratory technicians, monitoring will be carried out, the intervention will be documented and continuous feedback between clinicians and laboratory technicians will be ensured.

The implementation and results will be evaluated based on the RE-AIM conceptual framework of five domains: reach (comprehensiveness), efficacy, adoption (acceptability and representativeness), implementation and maintenance (sustainability) of the intervention in hospitals.

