# To implement the technique of laboratory diagnosis of cryptococcosis using the China ink method in urine as a point of care in selected hospitals in three southern provinces of Mozambique.

This is a stepped wedge trial. Sampling will be non-probabilistic by convenience in relation to the study sites and purposive in relation to the participants.

The study will be carried out in six hospitals (MCH, MGH, JMGH, MPH, XPH, and CHC) over six months. The Adaptation Phase will be the beginning of the iteration with the new test, the healthcare professionals (clinicians in medical service and laboratory technicians assigned to the microbiology sector) adapt to the workflow associated with the intervention (Figure 2). During the three months of adaptation, the researcher will carry out training on the care, diagnosis and treatment of cryptococcosis using urine dye (5 to 20 ml of the sample) with intentionally selected healthcare professionals, the diagnostic guide tools will be provided and an information-sharing workflow will be established between the laboratory and the clinicians.

It's up to the clinician to decide which patients to ask for a urine sample to diagnose cryptococcosis and also to decide what clinical information to share with the laboratory according to each situation. We will provide the national health system with a resource for the diagnosis of cryptococcosis, instead of empirical treatment when routine treatment is not available. Therefore, the clinician is free to request routine or experimental testing. If the clinician decides to request a urine sample for the diagnosis of cryptococcosis, the laboratory will provide feedback according to the clinician's request in order to follow up on the patient.

The implementation of the diagnosis of cryptococcosis with Chinese ink using non-invasive urine samples at the selected sites will take place over 6 months. In this implementation phase, the health professionals assigned to the medical service with knowledge of the intervention (new test for cryptococcosis) will request that it be carried out by colleagues from the laboratory who have been previously trained in its execution. Throughout this phase (Figure 2) monitoring of clinicians' behaviour in relation to the use of the new diagnostic will take place and documentation of its implementation will be captured (Appendix V).

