# Evaluation of the RE-AIM-based implementation of the technique of laboratory diagnosis of cryptococcosis using the China ink method in urine as a point of care in southern Mozambique

This is a cross-sectional quantitative study aimed at measuring the contribution of the diagnosis introduced (intervention effect) in the six hospitals (MCH, MGH, JMGH, MPH, XPH and CHC) over three months. Sampling will be non-probabilistic, intentional with regard to the participants (healthcare professionals) and by convenience concerning the study sites.

In the Implementation Evaluation Phase (Post-implementation), during three months the implementation will be evaluated using the RE-AIM conceptual framework with five domains reach (comprehensiveness), effectiveness, adoption (acceptability and representativeness), implementation and maintenance (sustainability) of the intervention in the hospitals. Data collection will be based on previously prepared questionnaires and standardized scripts coupled to the REDCap platform loaded onto the tablet.

- Reach will be calculated through the proportion of individuals covered by the intervention (clinicians and laboratory technicians).
- Efficacy will be assessed by checking laboratory and clinical results, time to diagnosis and satisfaction of health professionals.

The study includes an evaluation at the beginning (baseline) pre-implementation and at the end post-implementation, where laboratory and clinical results, time to diagnosis and satisfaction of health professionals will be verified at both times. The efficacy of the intervention will therefore be evaluated before and after implementation. WHO recommendations will be consulted, which recommend screening and treatment to prevent complications from a cryptococcal infection. The test to be implemented will contribute to starting treatment on the same day as the consultation and based on the aetiological diagnosis.

- Adoption will be explored through the representativeness of the services that have adopted the implementation including sample flow, laboratory processing and feedback, use of scripts drawn up and made available during the intervention.
- A Likert scale will also be used to analyze the satisfaction of all health professionals covered by the intervention during the study period (clinicians and laboratory technicians).

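### The before/after comparison estimates the effect of a whole implementation package, but the protocol labels it the contribution of the urine India ink test

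*Protocol*

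**What the plan says.** Section 7.8 lists what comes with the new test. Besides training, "a flow of information will be created between laboratory technicians and clinicians", and "the definition of a cryptococcosis case will be standardized and diagnostic and treatment guidelines will be provided".

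Sub-study 2 in Section 7.9 puts these components in the adaptation phase: "The Adaptation Phase will be the beginning of the iteration with the new test". In that phase "the researcher will carry out training on the care, diagnosis and treatment of cryptococcosis using urine dye", and "the diagnostic guide tools will be provided and an information-sharing workflow will be established between the laboratory and the clinicians". The same sub-study then describes staff as knowing "the intervention (new test for cryptococcosis"), so the intervention is named as the test alone.

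Sub-study 3 in Section 7.9 is "aimed at measuring the contribution of the diagnosis introduced (intervention effect"). It measures efficacy at a pre-implementation baseline and again after implementation. The outcomes are laboratory and clinical results, how long diagnosis takes, and how satisfied staff are.

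Section 8 (Study limitation) names loss of participants and response bias. It does not mention that other components are introduced along with the test.

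**The concern.** Several of the accompanying components can change the outcomes by themselves. A feedback workflow can shorten the time to a result. A case definition and guidelines can change who is tested and when treatment begins. Training can change how satisfied staff are. Routine diagnosis continues throughout: sub-study 2 leaves the clinician free to order either the routine or the new test, and Section 9 says the sample type in force will not change. So part of an improvement could come through existing tests.

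At stake is what the trial may conclude. The abstract hopes the findings will help persuade the Ministry of Health to give priority to low-cost diagnosis on non-invasive samples. If a package effect is reported as the contribution of the technique, the reader is told something the planned comparison cannot show.

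**Working it through.** The protocol gives no effect size, sample size or power figure for this comparison, so there is none to reproduce. The question is what the design can identify.

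**Step 1: the planned before/after contrast.** Inputs: six hospitals and two occasions (Section 7.9, sub-study 3). Let P mark the accompanying components and T the urine test. For hospital i and occasion t,

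y(i,t) = a(i) + b·P(t) + d·T(t) + error.

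The baseline precedes adaptation and the second assessment follows implementation. So P = T = 0 before and P = T = 1 after, in every hospital, and the model collapses to

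y(i,t) = a(i) + (b + d)·T(t) + error.

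The design matrix has 6 hospital columns + 1 for P + 1 for T = 8 columns, and its rank is 7. Only the sum b + d is estimable. More participants or more tests would not change this.

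**Step 2: does the phased schedule separate the two?** From Table 1 in Section 7.1, the lag is the implementation month (I) minus the adaptation month (AD):

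| Hospital | AD | I | Lag (months) |
| --- | --- | --- | --- |
| MCH | 6 | 7 | 1 |
| MGH | 6 | 8 | 2 |
| JMGH | 7 | 9 | 2 |
| MPH | 7 | 10 | 3 |
| XPH | 8 | 11 | 3 |
| CHC | 8 | 12 | 4 |

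The table has 6 × 15 = 90 hospital-months: 30 control, 6 pre-implementation, 6 adaptation, 9 blank, 6 implementation and 33 follow-up. The lags sum to 1 + 2 + 2 + 3 + 3 + 4 = 15, which is the 6 adaptation plus 9 blank hospital-months.

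Now fit hospital and month effects to the monthly grid, with P = 1 from the adaptation month and T = 1 from the implementation month:

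- All 90 hospital-months: rank 20 without P and T, 21 with P, 22 with both. Algebraically the two can be told apart, but only through those 15 hospital-months.
- Without the pre-implementation, adaptation and blank months (90 − 6 − 6 − 9 = 69 left): rank 20 without P and T, with P, and with both. Control months end at month 6 and implementation begins at month 7, so the month effects absorb both indicators.

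**Step 3: is the lag used?** No. The protocol assigns no outcome measurement or analysis to the adaptation and blank months, and sub-study 3 states a before/after comparison. The situation is therefore that of Step 1.

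**The case against.** The strongest reply is that bundling is the point of an implementation study. The main objective is to evaluate implementation, and the adaptation framework in Section 6 includes training, fidelity monitoring and workflow adjustment. A ministry that adopted the test would also have to train staff, so the package effect is relevant to policy. All of this stands. A package effect is a legitimate target; the fault lies in naming it the contribution of the diagnosis.

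It can also be said that much of the package serves the urine test. The training is described as using urine dye, and laboratory feedback is described for the case where a urine sample is requested. That stands in part. The training still extends to care and treatment, and the case definition and treatment guidelines are not specific to urine.

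Some stronger readings are tempting but not supported:

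- A reader might infer that everything starts at the same moment. Table 1 puts adaptation 1 to 4 months before implementation.
- A reader might infer that a new case definition shifts the denominator of confirmed cases. The protocol says the definition will be standardised, not that it is new, and Annex IV asks whether a case-definition guide is available. No planned outcome uses suspected cases as its denominator, and reach is a proportion of staff.
- A reader might infer that the expected results in Section 9 credit the technique alone. They list staff training, more diagnostic opportunities and earlier treatment side by side.

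**Conclusion.** The concern holds as a matter of attribution. As written, sub-study 3 can estimate the combined effect of the test, training, case definition, guidelines and workflow, and cannot isolate the test. This follows from the stated contrast and needs no assumption about effect sizes. It does assume that the baseline precedes adaptation and that the final assessment follows implementation, as sub-study 3 and Table 1 indicate.

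The share of a change that would be due to the accompanying components is unknown. A reader might infer that most of it would be; the protocol contains nothing from which such a share could be calculated, and any figure would rest on invented inputs. The point does not make the study unworkable or the package effect uninteresting. It limits what may be claimed for the technique itself.

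**What to change.** 1. In sub-study 3, and where sub-study 2 equates the intervention with the test, define the effect as that of the implementation package: urine India ink plus training, case definition, guidelines and feedback workflow. Add to Section 8 that the effect of the technique alone cannot be separated from the rest.

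2. Report requests and positive results by test type (urine India ink, CrAg, CSF India ink, culture) before and after implementation. The variables table already lists test type under the first two objectives. Where positives are not captured by type, a tally from laboratory registers would be needed. Present the table as descriptive evidence of how much of the change came through the urine test. Routine tests are not a clean control series, because urine tests may replace them and interruptions in rapid-test supply (Section 1) also move their numbers.

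The cost is a few reworded sentences and one extra table. The downside is a more modest claim for the technique.

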**Analyzing - Qualitative data**

The researcher will collect qualitative data through semi-structured interviews administered to health professionals, lasting 25 minutes each, and recorded on a digital recorder.

The analysis of qualitative data will be based on Nvivo software version 12. A thematic analysis will be carried out, with room for the emergence of hypotheses and new theories in relation to the topic.

The recorded interviews will be transcribed in Word without altering their originality and classified into previously created categories. Participants will be anonymized using numbers and the initials of their names. Quality control of the transcripts will be carried out by comparing what has been written with the audio of the interview to ensure that no information has been omitted or added, thus guaranteeing the originality of the information.

NVivo software will be used to help organize and control the data and the study will also be supported by the DAP and RE-AIM conceptual frameworks. The text passages will be grouped into themes according to the conceptual frameworks.

**This qualitative component will generate the following constructs:**

i. Health professionals' knowledge of the burden of cryptococcosis in their hospital and in the country;

ii. Health professionals' knowledge of cryptococcosis diagnosis methods in their hospital;

iii. Perceived barriers to screening, diagnosis, and treatment of cryptococcosis in your hospital;

iv. Survey: Opportunities for the new diagnosis of cryptococcosis in your hospital.

**Quantitative data analysis**

Quantitative data will be analyzed using the R studio statistical package. Univariate descriptive analyses will be carried out (mean or median age, standard deviation and variance will be calculated), percentage frequencies of the following variables: tests requested, doctors/laboratory technicians who adhered to the intervention, chi-square to check for associations between the intervention/test and the variables (level of education of the professional, availability of the test, severity of the disease and gender) and logistic regression to estimate the relationship between adherence to the test and factors severity of the disease, work overload in the US/laboratory, level of education of the professional, shift, gender, availability of laboratory services.

A Likert scale will be used to assess the level of satisfaction of all those involved in the intervention (doctors and laboratory technicians) during the study period. And the frequencies of the information obtained will be calculated.

The results will be described and presented in tables and graphs using the Microsoft Excel program. A p-value of <0.05 will be considered significant.

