# Practices and challenges in the laboratory diagnosis of cryptococcosis in six hospitals in the three southern provinces of Mozambique.

This is a cross-sectional study with a mixed approach. The qualitative approach will be generic, where the current situation will be assessed before the intervention is implemented (Figure 2: Pre-implementation phase) in order to identify elements of the social, health, administrative, and structural context that may or may not favor the intervention in the local context.

The assessment of the current situation will be carried out in six hospitals (MCH, MGH, JMGH, MPH, XPH, and CHC) over three months. Sampling will be non-probabilistic, and intentional with regard to the participants and by convenience with regard to the study sites.

The data for this study will be obtained through semi-structured questionnaires (Annexes I, II, and IV) and interviews (Annex III) with health professionals from each hospital (clinicians from the medical service and microbiology laboratory technicians); and a list will be made of the equipment, existing material and a description of the cryptococcosis diagnoses currently carried out in each hospital involved in the study and to identify barriers and facilitators to implementing the technique of diagnosing cryptococcosis with urine samples.

The data will be analyzed using the R studio statistical package, where the following analyses will be carried out: descriptive analysis (calculating frequencies, mean or median, standard deviation, and variance); and chi-square to compare frequencies. The results will be described and presented in tables and graphs. A p-value of <0.05 will be considered significant.

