**Anexo II**  **Versão 04, Outubro 2023**

**QUESTIONÁRIO**

**Código ___ ___ ___/_______/_____/202___**

(RESPONSÁVEL DO LABORATÓRIO E TÉCNICOS**)**

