**ANÁLISE DA SITUAÇÃO ACTUAL**

| Código da US/LAB______ | Nível_____ | N^o^ de técnicos______ |
| --- | --- | --- |

1. **Com que frequência é efectuado o controlo de qualidade**

Sempre As vezes**** Nunca Não sei ****

1. **Indique o equipamento e material existente no seu laboratório**

Incubador  Cabine de biossegurança  Centrifuga  Microscópio  Lâminas microscópicas  Lamelas  Geleira 

1. **Qual é a condição da infraestrutura?**

Adequado  Inadequado 

1. **Com que frequência o laboratório tem material/equipamento para teste de criptococose?**

Sempre As vezes**** Nunca Não sei ****

1. **Com que frequência o laboratório tem reagentes para teste de criptococose?**

Sempre As vezes**** Nunca Não sei ****

1. **Estima o número de amostras para o diagnóstico da criptococose que são processadas por semana no seu laboratório**

<10 10 -- 20 ≥30

1. **Com que frequência em amostras suspeitos, é diagnosticado *Criptococcus* spp no seu laboratório?**

 100%  80 – 99% 50 – 79%  <50%

1. **Considera a criptococose uma doença negligenciada em Moçambique?**

Sim Não  Não sei 

1. **Seu laboratório sofre atrasos na emissão resultados ou interrompe o processamento das amostras devido à falta de reagentes?**

Sim  Não  Não sei 

1. **Você sente que a qualidade do trabalho é consistente em todos os turnos? (horário de trabalho, fim de semana, feriado, plantão noturno)**

Sim Não

1. **Se NÃO, na sua opinião em qual turno a qualidade do serviço do laboratório é comprometida?**

Horário de trabalho Fim de semana Feriado Plantão noturno

1. **Com que frequência você recebe treinamento em microscopia?**

1 treino/ano 2 treinos/ano nunca fui treinado

1. **Quando foi o seu último treino?**

>6 meses  ≥1 ano  ≥2 anos

1. **Indique por favor o seu nível de instrução**

Médico especialista  Médico generalista  Enfermeiro Técnico de Laboratório

1. **No laboratório existe base de dados eletrónico e funcional?**

Sim  Não  Não sei 

1. **Existe no laboratório livro de registo de dados?**

Sim  Não  Não sei ****

1. **O laboratório tem critérios para rejeição de amostras**

Sim  Não **** Não sei ****

1. **Que tipo de amostras são processadas no laboratório?**

Sangue Urina LCR Expetoração Biopsia

Outras (por favor especifique)_____________________________

1. **Com que frequência tem o EPI disponível (luvas) para manuseamento das amostras?**

Sempre As vezes Nunca Não sei 

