**(Práticas/conduta _Clínico)**

1. **Indique o principal método de diagnóstico de criptococoses em uso no seu laboratório**

Clinico ; Tinta da China ; CrAg ; Cultura ; Teste de aglutinação em latex (TAL) ; Ensaio imune enzimático (EIE); PCR

1. **Com que frequência solicitas o teste?**

Sempre As vezes**** Nunca Não sei ****

1. **Com que frequência o teste de *Criptococcus* esta disponível?**

Sempre As vezes**** Nunca Não sei ****

1. **Tempo de resposta do Laboratório** (forneça sua melhor estimativa)

______min _______horas

1. **Tempo de início de tratamento após o resultado positivo** (forneça sua melhor estimativa)

______horas ______dias

1. **Considera a criptococose uma doença negligenciada em Moçambique?**

Sim Não 

1. **Antes de solicitar o teste que factores considera? (**pode escolher mais do que uma resposta)

**** Gravidade da doença

 Carga do trabalho na clínica/laboratório

 Idade do Paciente

 Disponibilidade de serviços de laboratório

CD4<100cell/mm^3^

CD4<100cell/mm^3^

 Outro (Faz favor mencionar):____________________________________________

1. **Qual é a sua opinião sobre o formulário de solicitação dos enxames laboratoriais?**

Adequado  Inadequado 

1. **O laboratório notifica as enfermarias quando há introdução de um novo exame incluindo os seus parâmetros?**

Sim Não

1. **O laboratório notifica imediatamente os resultados críticos**

Sim Não

1. **Com que frequência o laboratório avisa a você quando há interrupção de um determinado exame?**

Sempre As vezes Nunca Não sei 

1. **Você sente que a qualidade do trabalho é consistente em todos os turnos? (horário de trabalho, fim de semana, feriado, plantão noturno)**

Sim Não

1. **Se NÃO, na sua opinião em qual turno a qualidade do serviço é comprometida?**

Horário de trabalho Fim de semana Feriado Plantão noturno

1. **Quantos pacientes assiste por semana? (forneça sua melhor estimativa)**

<10 10 - 20 ≥30

1. **Qual é o perfil do paciente que chega á US**

Crítico moderado

1. **Assinale os sinais/sintomas da criptococose que observas nos seus pacientes**

cefaleia febre rigidez da nuca convulsões acne

Outro (por favor mencione):__________________________

1. **Existem critérios para triagem?**

Sim  Não 

1. **Guião de definição de caso disponível**

Sim  Não 

1. **O rastreio de criptococose em pacientes HIV faz parte da rotina na sua US?**

Sim  Não 

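### Items that describe the hospital are asked of each staff member and tested by plain chi-square, so answers from six hospitals are treated as 24 or more independent observations

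*Protocol*

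**What the plan says.** In the Protocol, Quantitative data analysis lists "chi-square to check for associations between the intervention/test and the variables (level of education of the professional, availability of the test" among its tests and closes with the rule "A p-value of <0.05 will be considered significant".

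Sub-study 1 (section 7.9, practices and challenges) takes its data from "semi-structured questionnaires (Annexes I, II, and IV) and interviews (Annex III) with health professionals from each hospital" and analyses them by descriptive statistics "and chi-square to compare frequencies". The table under Variables and data analysis plan lists availability of tests, reagent, microscope and centrifuge among the variables for this objective.

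The hospital-level items are spread over three annexes:
- **Annex IV (clinicians)** includes "Indique o principal método de diagnóstico de criptococoses em uso no seu laboratório" and an item on how often the Cryptococcus test is available.
- **Annex II**, addressed to "RESPONSÁVEL DO LABORATÓRIO E TÉCNICOS", includes "Com que frequência o laboratório tem reagentes para teste de criptococose", the tests available and the samples processed per week.
- **Annex V** puts one identical item, on whether the urine test has always been available in the hospital, to clinicians and technicians.

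Sample and Sampling lists the staff hospital by hospital, beginning "MCH: 8 clinicians from Medicine and 2 laboratory technicians". No section reduces the facility answers to one per hospital, and no chi-square allows for the grouping of staff within hospitals. Hospital level and health unit appear only as covariates in the regressions for the second and third objectives.

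**The concern.** Whether a laboratory has a test, and which method it mainly uses, is a property of that laboratory. When eight clinicians at MCH report it, that is mostly one piece of information reported eight times. A plain chi-square assumes independent observations, so it treats the repetition as evidence.

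Two things follow:
- Percentages for these items are weighted by the number of staff at each hospital and do not describe hospitals.
- The p<0.05 rule can declare an association that six hospitals cannot support.

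Sub-study 1 is meant to identify contextual elements that help or hinder the intervention. A barrier percentage dominated by the one quaternary hospital, or a spurious link, could mislead readers about the other five.

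**Working it through.** The Protocol gives no sample-size or power figure for these tests, so there is nothing to reproduce.

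**Inputs.** Headcounts are from Sample and Sampling. Clinicians: 8+4+4+3+3+2 = 24. Technicians: 6×2 = 12. Total: 36. Within-hospital agreement, ICC and the share of hospitals positive on an item are not in the document. They are assumptions, shown as ranges.

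**Weighting.** MCH carries 8/24 = 33% of clinician answers and CHC 2/24 = 8%. Each would be 1/6 = 17% if hospitals were described.

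**Effective sample size.** n/(1 + (m̃ − 1)×ICC), with m̃ = Σm²/Σm.
- 24 clinicians: m̃ = 118/24 = 4.92. At ICC 1 the result is 576/118 = 4.9; at 0.5 it is 24/2.96 = 8.1; at 0.3 it is 24/2.17 = 11.0.
- All 36 (10, 6, 6, 5, 5, 4; Annex V item): m̃ = 238/36 = 6.61. At ICC 1 the result is 1296/238 = 5.4; at 0.3 it is 13.4.

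**False-positive rate of the nominal 5% test.** Simulated 2×2 tables, 24 clinicians, no true association, 3 of 6 hospitals positive on each hospital fact.

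| Table | Uncorrected | Continuity-corrected |
|---|---|---|
| Two hospital facts, staff agree fully | 48% | 32% |
| Two hospital facts, each answer right 90% of the time | 26% | 15% |
| Two hospital facts, each answer right 80% of the time | 13% | 6% |
| One hospital fact v an answer with ICC 0.2 | 15% | 7% |
| One hospital fact v an answer with ICC 0.1 | 10% | 4% |
| One hospital fact v an answer with ICC 0.05 | 8% | 3% |
| One hospital fact v an unclustered answer | about 5-6% | about 2% |

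For the 12 technicians the uncorrected rates for two hospital facts are about 10%, 11% and 8% at full, 90% and 80% agreement. With correction they fall to 4% and 1% at 90% and 80%.

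**What six hospitals can show.** With a 3 v 3 split on both facts, the smallest two-sided Fisher p is 2/C(6,3) = 2/20 = 0.10, so p<0.05 is out of reach. Counted by clinician, the same perfect split gives chi-square = 24 and p of about 1 in a million.

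**The case against.** Several points on the other side have weight.

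- **A hospital-level record is partly planned.** Section 7.8 and sub-study 1 promise an equipment list and a description of the diagnoses carried out in each hospital, and section 7.8 adds an observation guide. A reader might infer that no such record exists; that would be wrong. But it is not linked to the chi-square tests. It mainly makes the fix easier.
- **The worst table is not named.** For the first objective, the variables table specifies chi-square of education and gender against the type of test requested, which are largely personal variables. Availability against method in use is permitted by the general wording in sub-study 1, but it is not prescribed. The 32-48% rate belongs to that kind of table only.
- **The items differ between forms.** A reader might infer that every facility item goes to all 36 people. At baseline, reagent frequency and samples per week are in Annex II only, and method in use is in Annex IV only. A count of 36 arises for the shared Annex V item, or if forms are pooled.
- **Some answers are perceptions.** Availability is rated on a frequency scale, and response time and sample volume are estimates. Colleagues can legitimately differ, which is why agreement below 100% is shown.
- **The correction matters.** R, the named software, applies a continuity correction to 2×2 tables by default, and this lowers the rates by a third or more. It does not apply to larger tables, and the availability item has four answer options.
- **The unit is inferred.** The Protocol never states the unit of analysis, and the headcounts stand under the qualitative component. No other sample is given for the questionnaires, however, and a plain chi-square on questionnaire answers implies the respondent as unit.
- **The consequence is limited.** No decision is tied to a chi-square result, and the before-and-after comparison in sub-study 3 rests on other measures.

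These points reduce the size of the problem. They do not remove it for facility items.

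**Conclusion.** The concern holds for items that describe the hospital. The Protocol itself fixes the test, one of the variables and the threshold, so this is not a detail left to a statistical analysis plan.

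The size depends on the table. Inflation is serious when both variables are hospital facts and staff largely agree. It is modest, or absent with continuity correction, when the other variable is weakly clustered, and immaterial when it is unclustered. The rates assume 24 clinicians, 2×2 tables and 3 of 6 hospitals positive. The weighting problem needs no p-value and affects any staff-level percentage of a facility item.

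A reader might infer that all of the plan's chi-square tests are invalid. The documents do not support that: education or gender against a clinician's own requests is a person-level question, inflated only so far as both variables cluster by hospital.

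**What to change.** In Quantitative data analysis, sub-study 1 and the variables table, make the hospital the unit for facility items: test availability, method in use, reagents, equipment and samples per week.

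- Build one record per hospital from the observation guide and the per-hospital description already planned. Report it as k of 6 hospitals in a six-row table, without a chi-square p-value.
- Where several staff of one hospital answer the same item, report how far they agree.
- Keep staff-level frequencies for personal attributes and opinions, and label ratings of availability as perceptions.

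This needs wording changes and one table, with no new data collection. The cost is that facility items will have no p-values.
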